### Ethics and dissemination

The protocol has obtained approval from the University of Rochester Research Subject Review Board.

#### Verbal consent for phone and in-person screening

When potential participants contact us, the study staff will first explain the study and obtain their verbal consent to proceed with phone screening, using the phone screening script. Compliance with HIPIAA authorization at the time of screening is being obtained through alternate HIPIAA language. A waiver of documentation of consent has been requested for this step because it is conducted over-the-phone so participants will not be able to sign this consent themselves.

#### Initial signed paper consent and re-consent

The initial signed paper consent will be obtained during the in-person interview by the subject.
Explanation of the study: During the in-person interview, the staff will explain the study in detail to the participants, including the study purpose, procedures, time commitment, randomization, data collection, risks, benefits, privacy, confidentiality, compensation, voluntary nature, and contact persons for questions and concerns. Emphasis will be placed on explaining the risks. Questions will be answered and any confusion about the study will be resolved.Assessment of capacity to consent: The staff will assess the potential intervention subject’s capacity to consent using the UCSD Brief Assessment of Capacity to Consent form (UBACC) for the study. A score of 2 on items 1, 2, 4, 6, 7, and 9 is needed for inclusion in the study. If a participant score is less than 2 on any item, the staff will re-explain the study and reevaluate the capacity of the subject. Given the potential fluctuation of their cognitive capacity, if a subject still fails to score 2 on required items, we will ask the person to return on another day to re-take the UBACC. If the subject still scores below 2 on any required item during the 2nd visit, he/she cannot be enrolled in the study. Of note, other items than the required 6 items are provided for education purpose. If they do not answer 2 on those items, the staff will re-explain the study, but such failures will not interfere with their eligibility in the study.

##### Ancillary and post-trial care

If the study team concerns about any participants’ mental health or safety, the study team may contact their primary care physician or other relevant health care provider. The study team will notify participants of these concerns prior to contacting their providers.

### Data analysis

#### Determine the intervention effect on outcomes

All primary analyses will follow *the intention-to-treat principle* (e.g., group assignment in the analysis will be based on randomized group assignment regardless of the level of adherence to provide unbiased comparisons of the effects among the groups). This principle will account for any potential data loss. We will fit linear mixed-effect models for each outcome measure, accounting for repeated measures at baseline, post-intervention, and 6- and 12-month follow-up. The models will include fixed effects for data collection visit (categorical variable), group assignment (compare the combined group with other groups), visit and group interaction, respective baseline outcome measure, and covariates identified as being imbalanced among groups. Stepwise variable selection using Akaike Information Criteria will be used to select the fixed effects for inclusion. A random participant-specific effect will be included to account for correlation between visits in the same participant. The model-based average within-group change in outcome measure for each group will be computed at each post-intervention and follow-up point. This will allow us to rank the groups in terms of average within-person gains in each outcome measure. In addition, *the effect sizes of RFB+VSOP and IR+VSOP control for each outcome measure* will also be calculated using standardized mean difference with 95% CI [(*M*_int_ − *M*_control_ at later time) − (*M*_int_ − *M*
_control_ at baseline)]/intra-participant standard deviation; “int” refers to combined intervention or VSOP; “control” here refers to attention control. The effect size of RFB+VSOP will be compared with that of the IR+VSOP control group to determine the additive effect.

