### Measures

#### ANS flexibility

ANS flexibility, the primary outcome, will be measured by CAN (central pathway) and HRV (peripheral pathway) at rest and in response to a challenging cognitive stressor, which we term the “stress task.” A protocol comprising rest and a stress task will be conducted within a 3T Prisma MRI scanner with both blood oxygenation level dependent (BOLD) fMRI and MRI compatible ECG monitored simultaneously. All measures for ANS flexibility will be collected at baseline, post-intervention, and 6- and 12-month follow-up.

*Auditory Consonant Trigrams* (ACT) [35, 36], a demanding working memory task, will serve as a cognitive stressor (see task paradigm in Fig. 1). Participants receive a three-consonant trigram (e.g., BME) verbally at a rate of one letter per second, followed immediately by a random three-digit number. Participants are asked to recall the trigram after a time delay (9, 18, or 36 s), during which they performed simple arithmetic aloud (counting backwards from the given number by 3’s) to minimize rehearsal effects. The task consists of five randomized trials for each time delay. The length of the task is 15 min. Before ACT, a 10-min acclimation (rest) period will be administered. We selected ACT as the cognitive stress task due to the high cognitive load that can simulate a cognitively demanding circumstance [35].

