**Fig. 1 Fig1:**
[figure not shown]
ACT task paradigm. Note. Letter stimuli will be auditorily instead of visually provided

*Electrocardiography (ECG) data* will be collected during rest and ACT task (both inside MRI) using PrismaFit MRI compatible ECG. Three disposable ECG electrodes will be placed in a lead-II configuration to record the ECG signal. A strain gauge will be secured around the lower chest to record respiration rate, and a pulse oximeter will be applied to the index finger to record pulse rate, which will both be considered as potential covariates in analyses using HRV. ECG signals will be conditioned and collected (1000 Hz sampling; 5 Hz for strain gauge) through an integrated A/D board and written to disk and later scored (with BIOPAC MRI compatible ECG processing software). The signals will be collected continuously during the BOLD imaging sequence. High-frequency heart rate variability (HF-HRV) data will be preprocessed with BIOPAC, using methods described previously [37]. Briefly, consecutive R-R intervals will be preprocessed using a filter at 0.12–0.40Hz for generating HF-HRV, and natural log transformation will be applied. We will process 30–60-s segments [to be consistent with BOLD dynamic functional connectivity (FC) analysis time window size] and remove ectopic beats and artifacts by consistent visual inspection between two raters. The first and last four segments, as well as incomplete segments (i.e., <15 s), of each recording at rest and task will be excluded from the analysis. Null values from motion and arrhythmic artifacts in the remaining data will be excluded by dividing the number of null-absent segments by the total number of segments to obtain the percentage of usable data for each participant. A threshold at 70% will be applied to determine subjects with valid rest and task data.

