*Analysis of weekly in-lab resting and task-related ECG data*: Degree of similarity between candidate ECG features (sliding window based 2-min segments) and previously revealed ECG shapelet will be calculated for each in-lab session. In our previous study, a higher degree of similarity to the ECG shapelet was related to worse learning from VSOP [11]. Here, we will model the trajectory of degree of similarity across in-lab sessions and calculate the relationship between the slope of trajectory and intervention effects on outcomes. If the combined intervention has greater, additive effects, compared to other groups, on outcomes, we expect to see a stronger relationship between the training process data and changes of main outcomes in the combined intervention group.

Cognition (primary outcome), NPS, IADL, and neurodegeneration (secondary outcomes) will be collected at baseline, post-intervention, and 6- and 12-month follow-up. Blood biomarkers (other outcomes) will be collected at baseline, post-intervention, and 12-month follow-up. All these measures together are considered as the markers of the progress of dementia.

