### Sample size

Sample estimation is based on the effect of RFB+VSOP combined intervention on two primary outcomes (ANS flexibility and cognition/IADL) by comparing to other groups (IR+VSOP control and IR control only). Literature indicates the following information related to deciding the effect size: (1) a moderate to large effect (using Hedges’ *g* = 0.83) of HRVB (including RFB) on stress regulation measures [17], (2) a small to moderate effect of VSOP on cognition, (3) correlation between ANS measures (*χ*^2^ = 11.70, *r* = 0.44) [7, 64], and (4) correlations between ANS measures and cognition (pooled *r* = 0.16) [65]. We estimate alpha = 0.025 (correct for two comparisons: combined intervention group with VSOP+IR control, as well as with the IR control group), and 3 measurement time points: baseline, post-intervention assessment, and 12-month follow-up. A sample size of 96 will be able to detect a small effect (*d* = 0.20). We further estimate a 20% attrition rate at the 12-month follow-up (in another local longitudinal study of cognitively healthy older adults [name] conducted [66], the attrition rate was less than 20% for up to a 5-year follow-up), and we will use a sample size of 114 (*n* = 38 per group).

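### Intention-to-treat is wrongly said to take care of data loss, and using baseline as both response and covariate costs precision and can drop participants from the HRV analysis

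*Protocol article*

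**What the plan says.** Under *Determine the intervention effect on outcomes*, the protocol article explains intention-to-treat in these terms: "group assignment in the analysis will be based on randomized group assignment regardless of the level of adherence". The next sentence adds: "This principle will account for any potential data loss".

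The section then specifies a linear mixed model with a random participant effect. Baseline is listed among the repeated measures, with the post-intervention, 6-month and 12-month visits. The fixed effects are visit, group, "visit and group interaction, respective baseline outcome measure, and covariates identified as being imbalanced among groups", and stepwise selection by AIC decides which stay.

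Other sections bear on this:

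- *Sample size*: "We further estimate a 20% attrition rate at the 12-month follow-up".
- *ANS flexibility*, electrocardiography paragraph: "A threshold at 70% will be applied to determine subjects with valid rest and task data". The ECG is scored after recording. HRV is one of the two components of ANS flexibility, a primary outcome; cognition is also primary.
- *Allocation*: randomisation follows completion of baseline data collection.
- *Blinding*: the analyses are to incorporate missing data, with no method or assumption given.

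**The concern.** The sentence credits intention-to-treat with a property it does not have. Keeping people in their assigned arm neither supplies nor adjusts for outcomes that were never observed. Protection against attrition comes from the likelihood-based mixed model, and only under missing at random. A reader who takes the sentence at face value would think the contrasts are safe from every kind of loss, in a trial that itself expects one participant in five to be missing at 12 months.

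The second problem is how baseline enters the model. As written it is both a response and a predictor of that response. A mixed model tolerates a missing response, but standard software drops every row with a missing covariate. A participant without a usable baseline HRV value would then lose all their follow-up HRV values too. That works against the aim of analysing everyone as randomised. The double role also makes the change-from-baseline contrast less precise than it need be.

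**Working it through.** **1. The plan's own figures for loss.** The base sample is 96, or 32 per arm. Then 32 × 1.2 = 38.4, truncated to 38, and 3 × 38 = 114, the stated total. At 20% attrition, 0.20 × 114 = 22.8 are missing at 12 months and 91.2 remain.

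**2. What protects against loss.** A simulation kept every participant in the assigned arm, with a true effect of 0 and about 20% loss at 12 months (two arms of 1,000, 25 replicates, within-person correlation 0.7, random-intercept model with baseline covariate). All settings except the 20% are assumptions.

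| Mechanism of loss | 12-month estimate, SD (Monte Carlo SE) |
|---|---|
| Completely at random | 0.005 (0.007) |
| At random, given observed outcomes | 0.005 (0.007) |
| Not at random, in one arm only | 0.075 (0.007) |

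Assignment was respected in all three rows. Only the mechanism changed, so intention-to-treat is not what gives the protection.

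**3. Loss through the covariate.** In a trial fit with 11 of 114 baseline values missing, a standard mixed model with baseline as covariate used 114 − 11 = 103 participants. The article gives no failure rate for the 70% rule. If a share q of baseline recordings fails (assumption), 114 × (1 − q) participants stay in the fit:

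| q | Participants with a valid baseline HRV |
|---|---|
| 5% | 108.3 |
| 10% | 102.6 |
| 20% | 91.2 |
| 30% | 79.8 |

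These losses come before attrition.

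**4. Precision.** The settings were 38 per arm, 20% loss at 12 months and an assumed within-person correlation of 0.6. The table gives the standard error of the 12-month contrast.

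| Baseline recordings | Baseline as response and covariate | Baseline as response only, common mean | Ratio |
|---|---|---|---|
| All valid | 0.218 | 0.200 | 0.218 / 0.200 = 1.09 |
| 20% invalid (assumed) | 0.247 | 0.207 | 0.247 / 0.207 = 1.19 |

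The variance ratios are 1.09² = 1.19 and 1.19² = 1.42.

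A hand check for the first row, with unit variance and correlation ρ = 0.6:

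- A change score has variance 2(1 − ρ) = 0.80. The contrast SE lies between √(2 × 0.80 / 38) = 0.205 with no loss and √(2 × 0.80 / 30.4) = 0.229 with 20% lost and nothing recovered from earlier visits.
- A baseline-adjusted value has variance 1 − ρ² = 0.64. The limits are √(2 × 0.64 / 38) = 0.184 and √(2 × 0.64 / 30.4) = 0.205.

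The simulated 0.218 and 0.200 fall inside these ranges. The penalty arises when the effect is read as change from baseline through the visit-by-group interaction, which fits the plan's use of average within-group change.

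**The case against.** **The model already does the work.** Right after the disputed sentence, the article specifies a mixed model over all visits, which was unbiased in both at-random rows above. This stands, and it is why the repair is mainly a matter of attribution. It does not rescue the sentence, which credits intention-to-treat and covers any loss.

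**Removal of participants is an inference.** The article does not say that a failed recording removes anyone from the model. AIC selection might drop the baseline term, and if baseline were read as a covariate only, complete baselines would bring no precision penalty of this kind. All fair. But the text lists baseline in both roles, and standard fitting has the consequences shown.

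**The 70% rule is a signal-quality rule.** A reader might infer that it breaks intention-to-treat, or removes randomised participants from the primary analysis at large. The documents do not support that. The rule is unrelated to arm or adherence and applies to HRV only. A failed follow-up recording may cost only that visit. No comparable validity exclusion is stated for scans or cognition, and cognition is collected before randomisation. What remains is the baseline ECG: it is scored later, and no validity check before randomisation is described.

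**Differential dropout.** A reader might also infer biased contrasts from unequal burden. The set-up of IR+VSOP mirrors the combined arm with IR in place of RFB, so burden is matched for the additive-effect comparison. It differs only against IR alone, where the number of contacts is still equal. The 0.075 SD puts all the not-at-random loss in one arm; equal departures with equal dropout would cancel.

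**Sensitivity analyses belong in the analysis plan.** Agreed. That plan is not shown, so the absence of one here is not a fault.

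**Conclusion.** The point holds in limited form. The statement about data loss is wrong as written and should be corrected whatever a separate analysis plan contains. The double role of baseline is a real specification fault. Under an assumed correlation of 0.6 it inflates the 12-month standard error by about 9% with complete baselines, and by about 19% if one baseline recording in five is unusable. The second figure also rests on complete-case fitting and on a failure rate that the article does not give. The possible exclusion of participants is confined to the HRV component of ANS flexibility.

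Nothing here shows that the trial's contrasts will be biased. The 0.075 SD illustration is 0.075 / 0.20 = 38% of the planned effect of 0.20, but it depends on an assumed mechanism. The comparison is also rough, because the analysis section standardises by the intra-participant SD, which need not be the scale of the planned effect.

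**What to change.** 1. Replace the sentence on data loss with wording such as: *participants are analysed in their randomised group; missing outcomes are handled by the mixed model under missing at random*.
2. Keep baseline as one of the repeated responses, with a common baseline mean across arms, and remove it from the covariates. Every randomised participant with any valid value then contributes, including those whose baseline HRV fails the 70% rule.
3. Optionally, add a delta-adjusted sensitivity analysis for the primary outcomes, to show how far departures from missing at random would have to go before the conclusion changed.

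The cost is one reworded sentence and a standard change of model form, with no change to data collection. The downside is a less absolute statement about data loss and, if the optional analysis is added, a result that may look less favourable.

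### Baseline is both a response and a covariate in one random-intercept model, and the tested contrast is not named: the test either runs above its nominal 2.5% or loses the precision of baseline adjustment

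*Protocol article*

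**What the plan says.** All of this is in the Protocol article, Data analysis, under Determine the intervention effect on outcomes.

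- **Response.** The mixed model is fitted to each outcome, "accounting for repeated measures at baseline, post-intervention, and 6- and 12-month follow-up". Baseline is one of four response visits.
- **Fixed effects.** "The models will include fixed effects for data collection visit (categorical variable), group assignment", followed by "visit and group interaction, respective baseline outcome measure, and covariates identified as being imbalanced among groups". The baseline value is also a covariate.
- **Correlation.** "A random participant-specific effect will be included to account for correlation between visits in the same participant". No other within-person structure is stated.
- **Selection.** "Stepwise variable selection using Akaike Information Criteria will be used to select the fixed effects for inclusion".
- **Reported quantities.** "The model-based average within-group change in outcome measure for each group will be computed at each post-intervention and follow-up point". An effect size "will also be calculated using standardized mean difference with 95% CI" is then defined as the between-group difference at the later time minus the between-group difference at baseline, divided by an intra-participant standard deviation.

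The section does not say which coefficient or contrast carries the hypothesis test. The Sample size section sets alpha at 0.025 for each of two comparisons and does not state sidedness.

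**The concern.** In the baseline rows the covariate equals the response, so those rows have no variation left once the covariate is in the model. Yet the model has one slope and one set of variance components for all four visits. The baseline rows pull the common slope towards 1 and pull the estimated variance down. A group difference read off at a follow-up visit then gets a standard error that is too small, which favours false positives.

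The covariate does no such damage to a change-from-baseline contrast, but it does no good there either. It is constant within a person and drops out.

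The same model serves every outcome, including the primary ones (ANS flexibility and cognition). The validity of the primary test thus depends on which line of output is read, and the plan does not settle that.

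**Working it through.** **Inputs.** From the article: 38 per group, four visits, alpha 0.025 per comparison (0.05/2 = 0.025, which reproduces the stated figure). Assumed: equal correlation rho between all visits, unit variance, complete data and a two-sided test (critical value 2.2414). The article gives no rho, so 0.2–0.9 is shown.

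**A. Adjusted group difference at a follow-up visit**

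1. The covariate is constant within person, so its slope comes from regressing the person mean on baseline: b = (1+3rho)/4. At rho = 0.7, b = 3.1/4 = 0.775.
2. True variance per person of the adjusted value: 1 − 2·b·rho + b². At 0.7: 1 − 1.085 + 0.6006 = 0.516.
3. Variance the model believes. The within-person part is 1 − rho. The between-person part is (1−rho)(9rho−1)/16, which is positive for rho > 1/9. The sum is (1−rho)(15+9rho)/16. At 0.7: 0.3 × 21.3/16 = 0.399.
4. Standard error ratio: √(0.399/0.516) = 0.88. With 38 per group, the model SE is √(2×0.399/38) = 0.145 and the true value is √(2×0.516/38) = 0.165.
5. Error rate: 2·[1 − Φ(2.2414 × 0.88)] = 4.9%.

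| rho (assumed) | SE ratio | Two-sided error at nominal 2.5% |
|---|---|---|
| 0.2 | 0.92 | 4.0% |
| 0.3 | 0.91 | 4.2% |
| 0.5 | 0.89 | 4.6% |
| 0.7 | 0.88 | 4.9% |
| 0.9 | 0.87 | 5.1% |

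REML simulation (three groups of 38, 3,000 runs per scenario) gave 5.3%, 5.6% and 5.9% at rho 0.5, 0.7 and 0.85 with complete data, and 4.8% at 0.7 with 20% dropout. If 0.025 is one-sided, the closed form gives 3.6–4.4%.

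**B. Visit-by-group change from baseline, same model**

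1. The true variance per person is 2(1−rho). The model's is twice its within-person variance, also 2(1−rho). The ratio is 1 (for rho > 1/9).
2. Simulated error at 12 months: 2.8–2.9% with complete data, 2.5% with 20% dropout (Monte Carlo error about 0.3 points). No inflation is shown.
3. Proper baseline adjustment has variance 1 − rho². The price of the change contrast is 2(1−rho)/(1−rho²) = 2/(1+rho): 2/1.7 = 1.18 at 0.7 and 2/1.5 = 1.33 at 0.5.

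**C. Using baseline once** (rho 0.7, equal correlation, 20% dropout)

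- Covariate only, follow-up visits as responses: error 2.1% at 12 months and 2.0% post-intervention; SE/SD 1.00.
- Response only: 2.5% for the 12-month difference and 1.9% for the change contrast; SE/SD 1.00 and 1.01. This run gave each arm its own baseline mean. It shows validity, not the precision gain that a common baseline mean would bring.

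**D. Random intercept under decaying correlation (a separate issue)**

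Assume AR(1) with 0.8 per visit step and complete data.

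1. The average of the six pairwise correlations is (3×0.8 + 2×0.64 + 0.512)/6 = 0.699, so the model variance of the 12-month change is 2(1 − 0.699) = 0.603.
2. The true variance is 2(1 − 0.512) = 0.976.
3. The SE ratio is √(0.603/0.976) = 0.786 and the error is 7.8%. The baseline covariate does not enter this calculation.

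A simulation with another decay pattern (0.7 to the power of half the visit lag) and 20% dropout gave 10.0% with the covariate and 9.1% without it for the same contrast. In that setting the covariate-only model with a random intercept still rejected at 6.0% for the 12-month difference.

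**The case against.** The strongest reply is that the inflated contrast is not one the plan names. Both quantities it describes, within-group change and an effect size built as later difference minus baseline difference, are changes from baseline. For those the redundant covariate does no harm to validity, and preferring covariance adjustment to change scores is a choice between two valid estimators. This stands, and it limits the point. A reader might infer that every standard error in the model is too small and that the primary analysis runs at double its nominal level. The article does not support that.

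It does not remove the point. The tested contrast is not named, and including the baseline value as a covariate points to an adjusted follow-up comparison as naturally as the effect-size formula points to change. On the harmless reading, a covariate that the plan specifies does nothing.

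A reader might also take the 8–10% error under decaying correlation as a result of the double use of baseline. It is not: with and without the covariate the figures are nearly the same.

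Two further objections stand in part. Correlation and sidedness are assumptions, so the size is a range. AIC selection might drop the covariate or the interaction; that was not simulated. Residual covariance may be left to an analysis plan that is not shown, so the covariance remark is a safeguard rather than an error found. The double use of baseline is different, because it is a stated rule.

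**Conclusion.** The point holds in conditional form. As stated, the model uses baseline twice and leaves the tested contrast open.

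- **Tested as an adjusted difference at a follow-up visit:** the standard error is about 8–13% too small, and the two-sided error is about 4–6% instead of 2.5%, for an assumed equal correlation of 0.2–0.9.
- **Tested as change from baseline, which the reported quantities suggest:** the error is near 2.5% under equal correlation, but the variance is 18% (rho 0.7) to 33% (rho 0.5) larger than with proper baseline adjustment.

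Neither is what a plan that specifies a baseline covariate should deliver. The exposure to decaying correlation (about 8% for the 12-month change contrast under the assumed AR(1) of 0.8) belongs to the single random intercept and remains whether or not the covariate is kept.

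**What to change.** 1. Use baseline once. Either (a) take only the post-intervention, 6-month and 12-month values as responses, with baseline as covariate plus visit, group and group-by-visit; or (b) keep baseline as a response with a common mean across arms and drop the baseline covariate. State which.
2. Name the group contrast and the visit that carry the test for each of the two comparisons.
3. Exclude the baseline term (under option b, the common-baseline-mean structure), group and group-by-visit from the AIC selection.
4. As a safeguard, specify an unstructured within-person covariance over the modelled visits in place of the single random intercept.

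Items 1 to 3 need a few sentences and no further participants or data. Item 4 costs a few extra parameters: 6 variances and covariances for three visits, or 10 for four, against 2 for a random intercept. The planned 114 participants can support that. The change should be made before unblinding.

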#### Concomitant care and interventions permitted or prohibited during the trial

We will exclude individuals who are having an experimental pharmacological or non-pharmacological intervention related to cognitive enhancement from enrolling in the study. After enrollment, any participation in such interventions concurrently will be discouraged. If any enrolled participants choose a concurrent experimental intervention, we will record the type of intervention. Any health care as usual will be permitted. The study is regularly recording and updating the type of care and experimental intervention, if any, from the participants, which may be addressed as covariates in later analyses.

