
*Covariates* will be assessed by collecting information on participants’ background characteristics (i.e., demographics), current medications, and subjects’ engagement in leisure activities and use of stress relief/relaxation-related activities outside of the study.

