### Allocation

Age (60–75 vs. 76–89) will be the factor for stratification. A block-based randomization strategy will be utilized. Co-I ([name]) will create a randomization schedule in REDCap using a random-number generator. Qualified participants will be randomized after completing baseline data collection. The study staff who is not conducting post-intervention assessments will conduct the randomization procedure.

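### The primary model picks its covariates from observed imbalance and stepwise AIC, does not name the age stratum, and leaves room for covariates measured after randomisation

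*Protocol article*

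**What the plan says.** Under Data analysis (Determine the intervention effect on outcomes), the protocol describes a linear mixed model for each outcome. Its fixed effects are visit, group, "visit and group interaction, respective baseline outcome measure" and "covariates identified as being imbalanced among groups". The next sentence reads: "Stepwise variable selection using Akaike Information Criteria will be used to select the fixed effects for inclusion". The section gives no criterion for imbalance, no candidate list and no restriction to baseline values.

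Under Allocation: "Age (60–75 vs. 76–89) will be the factor for stratification". No other stratification factor is named, and age does not appear among the fixed effects. Randomisation follows baseline data collection.

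Three other places name possible covariates:

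- Measures, ECG data: respiration rate and pulse rate are recorded with the ECG, "which will both be considered as potential covariates in analyses using HRV". Measures of autonomic flexibility, a primary outcome that includes HRV, are taken at baseline, post-intervention, 6 months and 12 months.
- Concomitant care: care and experimental interventions are recorded and updated during the trial, "which may be addressed as covariates in later analyses".
- Measures, Covariates: demographics, medications, leisure activities and "use of stress relief/relaxation-related activities outside of the study". The time of measurement is not given.

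**The concern.** In a properly randomised trial, a baseline difference between groups is chance. Its size says nothing about whether the variable predicts the outcome, and prediction is the reason to adjust. An imbalance rule followed by stepwise AIC lets the observed data decide which model is primary, and the answer can differ from one outcome to the next.

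The rule also works against the variable that the design singled out. Stratified blocks keep the two age bands close to balanced, so age group is unlikely to be picked up as imbalanced.

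Finally, nothing in the analysis section confines covariates to values fixed before randomisation. If a covariate that treatment can change enters an efficacy model, the estimate is no longer the plain randomised comparison that the intention-to-treat statement promises.

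**Working it through.** The plan gives no figure for this rule, so there is none to reproduce. Four checks follow.

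**1. How often an imbalance rule fires by chance.** Assumptions: k independent baseline variables, each screened at 5%. The protocol states neither the number nor the threshold.

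- P(at least one flagged) = 1 − 0.95^k
- k = 5: 0.23. k = 8: 0.34. k = 10: 0.40

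This measures how often the model would change under correct randomisation. It does not measure bias.

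**2. Precision lost by leaving out the age stratum.** Assumption: age group explains a share R² of the residual variance.

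- SE with age ÷ SE without age = √(1 − R²)
- R² = 0.05: √0.95 = 0.975, about 2.5% smaller
- R² = 0.10: √0.90 = 0.949, about 5% smaller

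**3. Error rate when the age stratum is left out.** Inputs: alpha 0.025 per comparison and 96 evaluable participants (Sample size), so 96 ÷ 3 = 32 per arm. The test is assumed two-sided, because the protocol does not say, and the strata are assumed equal in size. The critical value is z = 2.24.

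- Actual type I error ≈ 2 × [1 − Φ(2.24 ÷ √(1 − R²))]

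| Assumed share of outcome variance due to age | Closed form, age omitted | Simulated, age omitted | Simulated, age included |
|---|---|---|---|
| 5% | 0.021 | 0.022 | 0.025 |
| 15% | 0.015 | 0.016 | 0.026 |
| 30% | 0.007 | 0.008 | 0.025 |

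The simulation used 100,000 replicates of a single-visit comparison without a baseline-outcome term. Omission makes the test conservative, and inclusion restores the nominal level.

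**4. Follow-up respiration as a covariate.**

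- Three of the four scheduled recordings (post-intervention, 6 and 12 months) come after randomisation.
- RFB consists of training a breathing rate, so follow-up respiration can be a consequence of treatment.
- Rates tried when finding the resonance frequency (RFB overview): 4.5 to 6.5 breaths per minute. Divided by 60, this is 0.075 to 0.108 Hz.
- High-frequency HRV filter (ECG data): 0.12 to 0.40 Hz. Multiplied by 60, this is 7.2 to 24 breaths per minute.

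The trained rates lie wholly below the band in which HRV is measured. If training carried over to breathing near those rates in the scanner, respiratory power could leave the band and measured high-frequency HRV could fall. If breathing slowed but stayed within the band, or if HRV rose by another route, the result could differ. The sign of any bias from adjustment is therefore open.

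**The case against.** The strongest reply is that the post-randomisation part rests on permissions. Respiration and pulse are only potential covariates, and the text does not place them in the primary model; the protocol also has separate analyses of change in autonomic measures. Concurrent care may be used only in later analyses, and outside activities carry no time of measurement. Respiration has a measurement rationale too, since the stress task involves counting aloud. All of this stands. It limits the point to what the text leaves open.

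A reader might infer that the plan will adjust follow-up HRV for follow-up breathing and so shrink the RFB effect towards zero. The document supports neither step: adjustment is not prescribed, the frequency bands leave the direction unsettled, and no share of the effect running through breathing rate is given from which to size it.

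On age, the Blinding section says that the analyses will take account of the design features. Stratification could be meant, but the examples given are repeated measures and missing data, and the model that is actually listed omits age. A reader might also infer that age can never enter the model, or that omitting it inflates false positives. Neither holds. Only two broad bands are balanced by design, age within a band can differ by chance, and demographics are listed covariates. Omission makes the test conservative.

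It is also true that one baseline covariate entering by chance does not in itself bias a randomised comparison. The objection there is to a primary model chosen from the data.

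Full covariate lists are commonly left to a statistical analysis plan. This point does not ask for a missing list. It concerns a selection rule that the protocol states, which an analysis plan would have to follow or contradict.

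**Conclusion.** The point holds in a limited form. The stated rule makes the primary model depend on the data, first through observed imbalance and then through stepwise AIC, and the only stratification factor is not a named term.

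The age omission is small in effect: about 2.5% to 5% of the standard error if age explains an assumed 5% to 10% of residual variance, with a test that is somewhat conservative. The 34% to 40% chance that something is flagged rests on an assumed 8 to 10 independent variables screened at 5%, and shows only how readily the model would change.

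The document also leaves room for post-randomisation covariates in HRV analyses. Using follow-up respiration in an efficacy model would change the estimand and could bias the randomised comparison. Neither the direction nor the size can be given from the document. The change is worth making because it costs almost nothing and affects no sample size.

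**What to change.** In the analysis section, for the primary models:

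- Replace the imbalance phrase with a fixed set of terms: visit, group, visit by group, baseline outcome and age stratum (60–75 v 76–89).
- Delete the stepwise AIC sentence. It exempts none of the listed fixed effects, so an age term written into the model could be dropped again.
- State that only values obtained before randomisation may be covariates in efficacy models.
- Move follow-up respiration rate, pulse rate and concurrent interventions to analyses labelled as mechanistic or sensitivity. State when outside relaxation and leisure activities are measured, and treat any follow-up values in the same way.

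The sentences on ECG covariates and concomitant care should then point to those labelled analyses. The cost is a few sentences, with no change to sample size, visits or data collection. The downside is that a chance imbalance in another baseline variable is handled only in a sensitivity analysis.
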